## Adjustment

As the randomisation is stratified for gestational age all the statistical analyses will adjust for this factor. All main results will be presented overall and separately for girls and boys since a strong sex-differential effect of vaccines on mortality and hospitalisations has previously been found

# Statistics

**Data source:** Ages and Stages Questionnaire

**Primary outcome:** Age-adjusted sum score of ASQ at 13 months.

**Secondary outcomes:** Sub-scale scores (communication, fine motor, gross motor, problem solving, personal and social development).

**Sensitivity analyses:**

We expect to have data on approx. 85% of enrolled children. Some of these data may be incomplete. The ASQ manual suggests that partially completed scores can be used to impute the total score. The equation is: total ASQ score = sum of ASQ sub-scores / (300 - 10 * no. of missing)*300. In case of questionnaires less than 66% complete, they will count as missing. Sensitivity analyses using the simple imputation-data will be conducted.

Completely missing scores will be imputed using multiple imputations. Questionnaires less than 66% filled will be set to missing and then imputed.

Excluding children that did not follow the allocation.

**Exploratory outcomes:** Correlation of age-adjusted ASQ sum-score with sum of parent reported illness. Exploratory analyses will be presented with crude p-values not corrected for multiple comparisons.

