## Sub-study outcome

Ages and Stages Questionnaire (agesandstages.com): A validated, parent reported questionnaire concerning development in five domains: Communication, gross motor, fine motor, problem solving and social development. The questionnaire results in a combined score (0 - 300) that assesses the overall psychomotor development of the child. The questionnaire will be distributed to all parents of 13 months old children born at term (Appendix 1). Parents will automatically receive an email asking whether they would like to participate in this sub-study when the child is approximately 12.5 months old. The email will contain a link that directs to a web based version of ASQ and parents type the information directly into the electronic case report form.

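### Pro-rating and the 66% completeness rule are applied to the whole ASQ form rather than by domain, so a total can be produced with one domain blank while forms with three complete domains are set to missing: low impact, cheap to improve

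*Protocol*

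**What the plan says.** The section Sub-study outcome defines the instrument as "concerning development in five domains: Communication, gross motor, fine motor, problem solving and social development", and adds: "The questionnaire results in a combined score (0 - 300) that assesses the overall psychomotor development of the child". Under Statistics, the primary outcome is the age-adjusted sum score at 13 months, and the secondary outcomes are "Sub-scale scores (communication, fine motor, gross motor, problem solving, personal and social development".

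The handling of incomplete forms stands under Sensitivity analyses. Citing the ASQ manual, the protocol gives one formula for the total: "The equation is: total ASQ score = sum of ASQ sub-scores / (300 - 10 * no. of missing)*300". The threshold follows: "In case of questionnaires less than 66% complete, they will count as missing". Analyses of the data filled in this way are listed as sensitivity analyses. For the remaining gaps the protocol says "Completely missing scores will be imputed using multiple imputations" and "Questionnaires less than 66% filled will be set to missing and then imputed".

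Neither the formula nor the threshold carries a condition by domain.

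**The concern.** The outcomes are built from domains, but the rules for incomplete forms take no account of them. Dividing by the points available on the answered items, and scaling back to 300, gives every missing item the child's average over all answered items, whichever domain those belong to. If a whole domain is unanswered, the child still receives a total that is presented as covering five domains but rests on four.

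The threshold has the opposite fault. It can reject a form on which several domains are complete, because it looks only at the overall count.

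The sub-study is framed as a non-inferiority question with a safety element. A deficit limited to one domain is therefore a pattern the analysis should be able to show. Where that domain is the blank one, the pro-rated total cannot show it for that child. Where a form falls below the threshold, observed values of secondary outcomes may be replaced by imputed ones.

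**Working it through.** **Inputs.** Total range 0-300 and five domains (Sub-study outcome); the formula and the 66% threshold (Sensitivity analyses); SD 40, 2,000 children per group and a 5-point difference in means (Sample size considerations). *Assumption:* six items per domain, from an equal split of the items; the protocol does not state this.

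**The plan's own figure.** The stated power of about 97% reproduces. The standard error is 40 × √(2/2000) = 1.265; 5/1.265 = 3.95; 3.95 − 1.96 = 1.99, which gives 97.7% (two-sided α = 0.05). Nothing below depends on it.

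**1. Number of items.** 300/10 = 30; divided by 5 domains = 6 per domain, each domain scored 0-60.

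**2. What passes the threshold.** Completeness with m items missing is (30 − m)/30.

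| Form | m | Completeness | Result |
|---|---|---|---|
| One domain blank | 6 | 24/30 = 80% | scored |
| Ten items missing | 10 | 20/30 = 66.7% | scored |
| Eleven items missing | 11 | 19/30 = 63.3% | set to missing |
| Two domains blank, three complete | 12 | 18/30 = 60% | set to missing |

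The first row does not hinge on six items per domain: any domain of up to 10 items can be wholly blank and the form still passes.

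**3. Score with one domain blank.** Let S be the sum of the four answered domains. The formula gives S/(300 − 60) × 300 = 1.25 × S = S + S/4, so the blank domain is given the mean of the other four. With four domains at 40, S = 160 and the total is 160/240 × 300 = 200, whatever the fifth domain is:

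| True fifth domain | True total | Pro-rated total | Error |
|---|---|---|---|
| 20 | 180 | 200 | +20 |
| 40 | 200 | 200 | 0 |
| 60 | 220 | 200 | −20 |

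These are errors in one child's score, to be read against the SD of 40.

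**4. Effect on the group contrast.** Let BCG change domain j by δj, with total effect Δ = δ1 + … + δ5, and let a share p of forms in each arm lack domain 5. On those forms the pro-rated effect is 1.25 × (δ1 + δ2 + δ3 + δ4).

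- Effect spread evenly (each δj = Δ/5): 1.25 × 4Δ/5 = Δ. Recovered in full.
- Effect only in domain 5: 0 on those forms, so the contrast is (1 − p)Δ. The protocol does not give p. For p = 5-10% this is 0.95Δ to 0.90Δ; for Δ = 5 points, 4.75 to 4.50, a loss of 0.25 to 0.50 points.
- Effect only in one answered domain: 1.25Δ on those forms, so the contrast is (1 + 0.25p)Δ, or 1.0125Δ to 1.025Δ for the same p.

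The level error in step 3 comes from differences between domains. It cancels between randomised arms as long as the arms have the same share and kind of incomplete forms.

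**5. The same 66% applied within a domain.** 4/6 = 66.7% passes, 3/6 = 50% fails, and a blank domain (0%) fails. No blank domain can then enter a pro-rated total.

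**The case against.** The best defence is placement. The formula is listed for sensitivity analyses, and the protocol does not say that the main regression uses pro-rated totals. The rule is also bounded, since a form with two blank domains fails it and goes to multiple imputation. No rate of incomplete forms is given, and nothing suggests that incompleteness differs by arm. All of this stands and is why the impact is rated low. The formula is attributed to the ASQ manual, which is not at hand, so whether the manual pro-rates by form or by domain cannot be judged; the behaviour shown above follows from the formula itself.

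It may also be said that the alternative fills a blank domain from the other domains too. It does, but through a model that can allow for differences between domains and carries the uncertainty, rather than by assuming equal means.

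A reader might infer three stronger points that the protocol does not support:

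- *That partly answered sub-scales receive no valid score.* The formula yields only a total, but the protocol is silent on scoring a sub-scale with a blank item, and a statistical analysis plan may supply that rule.
- *That an error of 20 points in a child's total swamps the 5-point design difference.* One is an individual error, the other a difference in group means. The relevant figures are those in step 4.
- *That the web form lets parents skip items unprompted.* The protocol says only that "parents type the information directly into the electronic case report form". Whether a prompt exists is not stated.

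The discarding of complete domains is also a literal reading. The rule speaks of questionnaires and follows the formula for the total, so the authors may have meant it for the total alone.

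**Conclusion.** The point holds as a low-impact improvement to the sensitivity analyses. A form with one blank domain receives a total that carries no information on that domain, and, read literally, a form with three complete domains loses three observed secondary scores to imputation. The first statement needs only that no domain exceeds 10 items; the 80% and 60% figures rest on six items per domain.

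For the group comparison the demonstrated cost is small: none for an effect spread evenly over domains, and a dilution equal to the share of affected forms for an effect confined to the blank domain. The 5-10% range used for that share is an assumption. The main analysis, the sample size and the power are not called into question.

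**What to change.** In the sensitivity analyses, apply the existing 66% threshold within each domain. With six items, at least four must be answered; the domain score is then the sum of the answered items × 6 / number answered, and the total is the sum of the five domain scores. Where a domain falls below the threshold, set only that domain to missing and multiply impute it, with the child's observed domain scores in the imputation model. State that every observed sub-scale score is kept for the secondary analyses, whatever the completeness of the rest of the form. If the domains do not have six items each, restate the cut-off accordingly.

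The cost is a sentence or two in the protocol and slightly more scoring code. A few forms that are now simply pro-rated would need one domain imputed. Sample size and data collection do not change.

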**Statistical analysis:**

1. Regression analysis of ASQ scores with BCG, prematurity and age at follow-up as independent variables.
2. Secondary outcomes subject to post-hoc Holland correction.
3. If data are not reasonably normally distributed, we will present confidence intervals obtained by bootstrapping.

**Subgroup analyses:** Premature children, sex, BCG-immunisation within two days of birth. Subgroup analyses will be conducted in case of both statistically significant and statistically insignificant primary outcome.

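### The protocol assigns the pro-rated score for partly completed questionnaires to sensitivity analyses, so the primary analysis as written loses those children, and it discards observed answers before multiple imputation.

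*Protocol*

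**What the plan says.** The primary outcome, in the protocol's Statistics section, is "Age-adjusted sum score of ASQ at 13 months". The analysis, under Statistical analysis, is "Regression analysis of ASQ scores with BCG, prematurity and age at follow-up as independent variables". Neither place says how a questionnaire with blank items is scored.

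Partial forms are handled under the heading Sensitivity analyses. The protocol expects data on about 85% of enrolled children and accepts that some forms will be incomplete. It continues:

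- Source of the rule: "The ASQ manual suggests that partially completed scores can be used to impute the total score".
- Formula: "total ASQ score = sum of ASQ sub-scores / (300 - 10 * no. of missing)*300".
- Lower limit: "In case of questionnaires less than 66% complete, they will count as missing".
- Use: "Sensitivity analyses using the simple imputation-data will be conducted".
- Multiple imputation, under the same heading, covers completely missing scores and the sparser forms: "Questionnaires less than 66% filled will be set to missing and then imputed".

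**The concern.** A sum score over 30 items is undefined once one item is blank, unless the plan says how to complete it. The protocol has such a rule and attributes it to the instrument's manual, but assigns its output to sensitivity analyses. With no other rule for the primary score, the natural consequence is that only fully completed forms contribute to the primary result. A child with 29 of 30 items answered would then be left out, although the protocol itself regards that form as usable.

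The second part concerns forms below the 66% limit. Setting the form to missing before imputing treats a child with many answered items like a child with no form. A child's own answers on the same questionnaire are probably the best available predictors of that child's total.

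At stake are children who were randomised and followed up, and whose parents replied, but whose data do not reach the primary estimate or are removed before imputation.

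**Working it through.** **Inputs from the protocol**

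- 2000 term children per group, α = 0.05, SD 40, difference 5 points, power about 97% (Sample size considerations).
- Data expected on about 85% of children; pro-rating formula; 66% limit (Sensitivity analyses).
- Total score range 0 to 300 (Sub-study outcome).

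**Assumed, because the protocol does not give it:** the share of responders with at least one blank item on a form at least 66% complete, taken as 5%, 10% and 20%.

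**Step 1. What the formula implies.** Each missing item takes 10 points off a maximum of 300, so there are 300/10 = 30 items. The limit is 0.66 × 30 = 19.8. A form with 20 or more answers (up to 10 blanks) can be pro-rated. A form with 19 answers or fewer counts as missing.

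**Step 2. Reproduce the stated power.** With n per group, SE = 40 × √(2/n), and two-sided power is Φ(5/SE − 1.96).

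For n = 2000: SE = 1.265, 5/SE = 3.953, and Φ(1.993) = 97.7%. This agrees with the stated figure of about 97%. (The protocol does not say whether α is one- or two-sided; one-sided gives 99.0%.)

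**Step 3. Apply the protocol's own response rate.** 0.85 × 2000 = 1700 per group. This is the number available if partial forms are pro-rated and kept.

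**Step 4. Remove an assumed share of partial forms.**

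| Responders dropped | n per group | SE | 5/SE − 1.96 | Power |
|---|---|---|---|---|
| 0% (pro-rated and kept) | 1700 | 1.372 | 1.684 | 95.4% |
| 5% | 1615 | 1.408 | 1.592 | 94.4% |
| 10% | 1530 | 1.446 | 1.497 | 93.3% |
| 20% | 1360 | 1.534 | 1.300 | 90.3% |

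Power serves here only as a measure of precision.

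**Step 5. The imputation rule.** A form with 19 of 30 answers is 19/30 = 63% complete and falls under the limit. Taken literally, the rule sets all 19 answers aside before imputing. The protocol gives no basis for estimating how many children this affects, so no size is attached to this part.

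**The case against.** The strongest reply is that the 66% limit is a general scoring rule: the formula is given, sparser forms are excluded, and all other forms are scored by the formula in every analysis. No sentence says that partial forms are dropped. This reading is possible, but it leaves "Sensitivity analyses using the simple imputation-data will be conducted" with nothing to do, because a sensitivity analysis on data scored exactly as in the primary analysis tests nothing. What stands is that dropping the children is the consequence of the text as written, not a stated intention.

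A second reply is that the imputation model is normally specified in a statistical analysis plan, which is not at hand, and that only the total might be set to missing while the items remain as predictors. That may be the intention. The sentence, however, speaks of questionnaires being set to missing, and its plain sense removes the answers.

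Third, the loss of precision is small. This stands in full: even with 20% of responders dropped, power stays above 90%.

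Fourth, pro-rating is not neutral. If parents skip items that their child cannot yet do, the scaled total is too high; an analysis of completed forms would be selective for the same reason. The documents show neither. This is a reason to report both analyses, not to leave the primary rule unstated.

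A reader might also infer that blank items are summed as zero in the primary score. Nothing in the protocol supports this, and the formula, which shrinks the denominator for each blank, shows that the authors do not regard a blank as a zero.

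**Conclusion.** The point holds in a limited form. The protocol puts the pro-rated data in sensitivity analyses and gives the primary sum score no rule for partial forms. As written, children with forms at least 66% but not fully complete are lost from the primary analysis. It also states that forms under 66% complete are set to missing before imputation, which discards observed answers.

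The size is modest: 95.4% power with partial forms kept, against 94.4% to 90.3% without them. This rests on 85% response, SD 40, a two-sided α of 0.05 and an assumed 5% to 20% of partial forms. The case for change is that usable data are recovered at almost no cost, not that the trial is underpowered.

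Two stronger conclusions are not supported. A reader might infer that the comparison between the groups is biased, but that would need skipping to differ between the arms, and nothing in the documents indicates that it does. A reader might also take 5 points as a non-inferiority margin and judge the missing data against it; the protocol gives 5 points only as a difference to detect and names no margin.

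**What to change.** 1. In the primary outcome definition, state that questionnaires at least 66% complete are scored with the formula already quoted in the protocol.
2. Make the analysis restricted to fully completed questionnaires a sensitivity analysis.
3. In the multiple imputation, treat the total of a form under 66% complete as missing, but keep its observed item or domain scores as predictors.

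An analysis that shifts the imputed scores in the BCG group downwards could be added given the non-inferiority aim, but it is optional and does not correct an error in the text.

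The cost is a few lines of text and minor programming, best settled before outcomes are examined by group. The small downside is that the primary score then relies on the assumption that blank items would have scored like answered ones. The completed-forms analysis in item 2 shows whether the result depends on including the pro-rated forms.

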# Sample size considerations

The overall trial

The main trial includes 4300 children to be able to detect a 20% reduction in infant hospitalisation with 90% power and α = 0.05.

Sub-study

The entire Calmette-cohort will comprise 4300 children. Of these approximately 300 will be preterm (< 37 GA). Based on a sample size of 2000 mature children in each group, an α = 0.05, a mean ASQ score of 200 with a standard deviation (SD) of 40 this study will have a power of approximately 97% to detect a 5 points difference (effect size 0.12) between mean scores in BCG vaccinated children compared to unvaccinated children. When used for screening purposes, an ASQ score of ≥1.5 SD (approximately 60 points at age 13 months) below the mean is considered indication of developmental delay (13). The high power of this sub-study will allow meaningful exploratory subgroup analyses.

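### Multiple-imputation sensitivity analysis: forms under 66% complete are blanked before imputation, discarding answers that strongly predict the total (minor, cheap to mend)

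*Protocol*

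**What the plan says.** The rule stands in the Protocol, Statistics, under Sensitivity analyses. Data are expected for most but not all children ("We expect to have data on approx. 85% of enrolled children"), and the next sentence adds "Some of these data may be incomplete". Two devices follow:

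- **Simple pro-rating.** A partly filled form is scaled up to 300 points by the manual's equation, which removes 10 points from the denominator per missing item. Forms under 66% complete count as missing.
- **Multiple imputation.** This is used for scores that are wholly missing. Forms below the threshold join them: "Questionnaires less than 66% filled will be set to missing and then imputed".

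No imputation model or predictor list is given, and nothing says that answers on a blanked form are kept as predictors. The expected share of forms below the threshold is not stated. The secondary outcomes come from the same form: "Sub-scale scores (communication, fine motor, gross motor, problem solving, personal and social development"). The main analysis, under Statistical analysis, is a regression that does not mention imputation.

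**The concern.** A completeness threshold makes sense for pro-rating, where a few answers are scaled up to stand for the whole. It has no such purpose in multiple imputation, which can use whatever was answered. Read naturally, the rule deletes observed outcome data and then imputes the child as if nothing were known.

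Three things could be at stake:

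1. **Precision.** The deleted answers are the best available predictors of the unanswered ones.
2. **Secondary outcomes.** If the whole form is blanked, sub-scale scores that were fully observed disappear from this analysis.
3. **Bias, under conditions.** If parents of slower children stop part-way more often in one arm, the answers already given carry the information needed to correct for it, and blanking removes that information. The sub-study is framed as non-inferiority with a safety motive. The outcome is parent-reported, and the control group simply receives no vaccine. Selective stopping in the BCG arm would move the estimate in favour of BCG.

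**Working it through.** **The plan's own figure.** Sample size considerations takes 2000 term children per arm, a level of 0.05, a mean total of 200 and an SD of 40. The power it claims on that basis is "a power of approximately 97% to detect a 5 points difference (effect size 0.12"). Sidedness is not stated; two-sided is assumed.

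- SE = 40 × √(2/2000) = 1.265, so 5/1.265 − 1.960 = 1.993 and power is 97.7%. The stated figure is reproduced.
- At 85% of 2000 = 1700 per arm, SE = 40 × √(2/1700) = 1.372 and power is 95.4%.

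**What the threshold removes.** The total runs to 300 at 10 points per item, so there are 300/10 = 30 items. Five domains give 6 items each if equal (assumed). The cut-off is 0.66 × 30 = 19.8 items. Forms with 18 items (60%) or 19 items (63.3%) are blanked; a form with 20 items (66.7%) is kept. Up to three complete domains can therefore be lost.

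**How informative three domains are.** Assume five domains with equal variance s² and common correlation r.

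- Variance of the total: (5 + 20r)s².
- Variance of the last two domains given the first three: (2 + 2r − (6r)²/(3 + 6r))s².

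| r (assumed) | Unexplained share of variance | Residual SD = 40 × √share |
|---|---|---|
| 0.3 | 1.925/11 = 0.175 | 16.7 |
| 0.4 | 1.733/13 = 0.133 | 14.6 |
| 0.5 | 1.500/15 = 0.100 | 12.6 |

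After blanking, the SD for such a child is 40, apart from whatever age and baseline data explain.

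**Precision of the trial estimate.** Let f be the assumed share of returned forms under 66%, and R² = 0.85 for three complete domains. The approximate effective size per arm is 1700(1 − f) when blanked and 1700(1 − f) + 1700 × f × R² when kept. SE = 40 × √(2/n).

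| f | SE blanked | SE kept | Ratio | Power blanked | Power kept |
|---|---|---|---|---|---|
| 2% | 1.386 | 1.374 | 1.01 | 95.0% | 95.3% |
| 5% | 1.408 | 1.377 | 1.02 | 94.4% | 95.3% |
| 10% | 1.446 | 1.382 | 1.05 | 93.3% | 95.1% |

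Three complete domains is the most favourable case for keeping the answers. Parents who stop earlier leave less to recover.

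**Bias, by simulation.** There are 1700 per arm, no true effect, total SD 40 and r = 0.4. Parents stop after the third domain. Positive values favour BCG.

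Stopping related to the answers already given:

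- Equal in both arms: no bias beyond simulation error.
- Baseline shares 5% (control) and 8% (BCG), log-odds of stopping falling by 0.7 per SD of the answers in both arms: +0.8 when blanked, about 0 when kept (400 runs).
- Shares 3% and 2%, odds ratio 1.65 per SD in both arms: 0.2 when blanked.
- Odds ratio 2.7 against 1.65, shares 2–3%: 0.4–0.5 when blanked.
- Odds ratio 2.7 in the BCG arm and no dependence in controls: 0.3, 1.1, 1.8 and 3.4 when blanked, at shares of 1%, 3%, 5% and 10%.

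Stopping related to the unanswered domains, BCG arm only, 5% share: 1.5 when blanked, 0.5 when kept.

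Every share and odds ratio here is an assumption. For scale, the SE of the difference is about 1.4 and the planning difference is 5 points.

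**The case against.** The strongest reply has four parts.

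- **The text may be read more mildly.** Setting to missing could mean only that the total is not pro-rated below 66% and goes to multiple imputation instead, with the answered domains still available as predictors. The model may be in a statistical analysis plan that is not shown. This reading is possible, so it cannot be said that the draws will certainly ignore the answers. It is not the natural meaning of the sentence, however, and an analysis plan that follows the sentence would carry out the deletion.
- **The rule sits in a sensitivity analysis.** The main regression does not invoke it. This stands and limits the consequences.
- **The bias is hypothetical.** A reader might infer that the rule biases the comparison. The documents do not support that: bias in the difference needs stopping that is related to development and also differs by arm, and there is evidence of neither. The largest simulated values come from a one-sided scenario with up to 10% part-way forms. Nor is keeping the answers a full cure: the zero bias follows from assuming that stopping depends only on those answers.
- **The precision loss is small.** A reader might infer a large loss from an SD of 40 against 13 to 17. That contrast is per affected child; for the trial the loss is a few per cent at most over the shares considered. The roughly 15% of children expected to have no data are untouched by any change here.

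What remains is a stated step that discards informative data with no benefit to multiple imputation.

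**Conclusion.** The point holds as a minor one. As written, the rule discards up to three complete domains (assuming 6 items each) before a procedure able to use them. If applied to whole forms, it also removes observed values of secondary outcomes.

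The SE is about 1% higher at 2% such forms, 2% at 5% and 5% at 10%, under the assumed shares, R² = 0.85 and 1700 per arm. Bias in the BCG-control difference is conditional on arm-related, development-related stopping. In the moderate scenario of 5% against 8% it was about 0.8 points, or 0.8/5 = 16% of the planning difference. It was nil when stopping was alike in both arms. Keeping the answers removes this bias when stopping depends on the answers given, and only reduces it when stopping depends on unanswered items. The protocol's main result is not called into question.

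**What to change.** Confine the 66% threshold to the simple pro-rated score, and replace the sentence on blanking with wording such as: *In the multiple-imputation analysis no answered item is set to missing. Unanswered items or domains are imputed conditional on the child's answered items or domains, allocation, age at follow-up and baseline data, and the total is then formed.* Sub-scale scores that were observed then stay as observed.

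It would also help to report, by arm, the number of forms below the threshold, since that share decides whether the choice matters.

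The cost is a change of wording and a slightly more complex imputation model, at item or domain level instead of on the total. No new data are needed and nothing changes for parents.
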